## Abstract

**Background:**

Depression is one of the most common mental disorders with a high prevalence among the older adults. In recent years, after realizing some side effects of the antidepressants, non-pharmacological psychological treatments begin to attract accruing attention. Reminiscence therapy is one of the psychological treatments that specially designed for the elderly to improve their mental health status by recalling and assessing their existing memory. Though some studies indicate reminiscence therapy can be effective and beneficial for the mental health of elderly, the conclusions are not consistent yet. The aim of this research is to assess the effectiveness of reminiscence therapy for Chinese elderly.

**Methods:**

Sixty older adults (≥60 years of age) with mild to moderate depression will be randomly assigned to an experimental or a control condition. The participants in the experiment group will receive the reminiscence therapy under the Watt’s protocol with adaptation to Chinese Culture which consists of six weekly sessions of 90 minutes each. The control group will be treated as before. An assessor who is blind to intervention will conduct the measures before treatment, after treatment immediately, and three months after treatment.

**Discussion:**

This study will provide the evidence whether the reminiscence therapy is effective to treat depressive symptoms of Chinese elderly. This research has been registered in the clinicaltrials.gov (NCT01553669).

## Background

Aging population around the world is growing fast. As the United Nations Statistics Division shows, the elderly of the world was about 865 million in 2010, and will reach 2.008 billion in 2050 [1]. Moreover, according to National Bureau of Statistics of China, the Chinese elderly aged 60 and above were about 178 million in 2010, accounting for 13.26% of population [2]. With the increasing number and proportion of the elderly, the geriatric mental health problem becomes more important. Depression is one of the most common mental disorders found in the elderly. In our recent survey of Chinese elderly, the prevalence of self-reported depressive symptoms (CES-D≥16) reached to 39.86% [3]. Depression causes disability of functional impairment, reduces life satisfaction and quality, it is also associated with a high risk of suicidal behavior, and increases the burden and the costs of health and home care services [4-6]. Therefore, the appropriate early intervention for the elderly individual suffering depression is significant and critical [7,8].

At present, drug therapy and psychotherapy are two commonly used methods for the treatment of depression [9]. Depression is mainly treated by medication for a long time [10]. However, previous studies also indicated that pharmacologic approaches had numerous side effects [7,11-13]. In addition, the elderly cannot learn any skills from the drug therapy in protection against the relapse of depression [8]. Currently, increasing studies and reviews support the efficiency of psychotherapeutic treatment for depression. Cognitive or cognitive behavioral therapy [14-16], problem-solving therapy [17] and interpersonal therapy [18,19] are widely accepted as methods in reducing the depression. Based on traditional interventions, reminiscence therapy is specially recommended for geriatric depressive adults. This psychotherapy has been designed and developed because of the recognition of the unique needs and concerns involved in adaptation to the late stage of life [8].

### Reminiscence therapy

The theoretical framework of reminiscence therapy derived from Erikson’s theory of ego development [20]. Erikson divided life span into eight stages. In his theory, Erikson believed people would experience a main crisis or conflict in each stage, which served as a turning point in development and needed to be solved. For the elderly, the principle task is to achieve ego-integrity and avoid despair [21]. Erikson suggested that assessment of the past was an essential component in successful completion of this task [8]. Butler and Birren developed Erikson’s work and proposed that ego integrity could be achieved in an analytical and evaluative way to recall one’s past [22]. In recent years, researchers developed the continuity theory and contributed other insights in understanding the importance of reminiscence. According to continuity theory, when individuals encounter life-events which need them to change or convert, they will use adaptive strategy by linking present to their past experiences. This strategy is adopted to “preserve and maintain existing internal and external structures” and “produce continuity in inner psychological characteristics as well as in social behavior and in social circumstances” [23].

Reminiscence therapy is a method of using the memory to protect mental health and improve the quality of life. Reminiscence is not just to recall the past events or experiences. It is a structured process of systematically reflecting on one’s life with a focus on re-evaluation, resolving conflicts from the past, finding meaning in one’s life and assessing former adaptive coping responses [24-26]. Watt and Wong (1991) defined six types of reminiscence: integrative, instrumental, transmissive, narrative, escapist and obsessive [27]. They identified the integrative and instrumental reminiscence was related to adaptation and well-being among older adults, and developed the corresponding intervention manual [25].

In the last several decades, increasing studies indicated that reminiscence therapy is effective for the elderly with depression [26,28-33]. Besides alleviating the depression symptoms, reminiscence therapy was proved to improve self-esteem [34], life satisfaction [35], psychological well-being [36], personal mastery [37,38] and loneliness [39,40]. However, the conclusion is not consistent [41-43]. The reasons may be attributed as some studies did not follow randomized controlled trial (RCT) design, lack of strict protocol and had high dropout rates.

### Study purposes

The purpose of the research is to examine the effect of reminiscence therapy on depressive symptom, self-esteem, life satisfaction, and loneliness in Chinese elderly.

Specifically, the aims are:

Firstly, we intend to explore whether reminiscence therapy will significant improve the experiment group’s depressive symptom in comparison with control group after six weeks therapy, and whether the efficacy can be maintained during three-month follow-up.

Secondly, we are interested in whether reminiscence therapy is a potential effective treatment to reduce the loneliness, increase the self-esteem and life satisfaction for the experiment group elderly.

## Method

### Design

The trial will be conducted as a pre-post test compared and randomized controlled trial. After collection of the baseline test, research assistant will open a sealed sequential randomization envelope for each participant indicating either the “reminiscence therapy group” or the “waiting-list control group”. The envelopes have been prepared previously by the evaluator via a computerized randomized program. The assessments will be conducted by another evaluator who is not the therapist and is blind to the group assignment.

The reminiscence therapy group participants will receive six-week interventions, while the control group participants will not receive any emotional related treatment. After the intervention, all the participants will receive post-test. Then after three months, all the participants will receive the follow-up test. An overview of the study design is shown in Figure 1.

**Figure 1 F1:**
[figure not shown]
**An overview of the study design. **Abbreviations: GDS =Geriatric Depression Scale; MMSE = Mini-Mental State Examination;DSM-IV = Diagnostic and Statistical Manual of Mental Disorders, Fourth Edition; SES = Self-Esteem Scale; LSI-A = Life Satisfaction Index A; UCLA = Russell’s UCLA Loneliness Scale.

The research protocol has been approved by the Institutional Review Board of the Institute of Psychology, Chinese Academy of Sciences. Before signing a consent form to get into the research, the participants will be introduced about the procedure, the purpose and the objectives, the items we will use and the time needed of this study. They will be informed that they are free to withdraw at any time and we promise their personal information will never be released.

### Participants

A total of sixty subjects who fulfill the following inclusion and exclusion criteria will be recruited from the community.

#### Inclusion criteria

1) The age of participants is equal or over than 60 years old;

2) The score of the Geriatric Depression Scale (GDS) should fall between 10 and 26 points;

3) A score of 24 or higher on the Mini-Mental State Examination (MMSE);

4) Not taking anti-depressant medication or taking part in other psychotherapy when enrolling, or with stable anti-depressant medication for at least three months;

5) Having no problem with communication (such as, can speak fluent mandarin, or, his/her dialect can be understood by other participants or evaluators).

#### Exclusion criteria

1) Suicide attempt;

2) A diagnosis of cognitive impairment by DSM-IV, or mental disorders other than depression;

3) Alcohol or drug abuse;

4) Cannot grantee attending the therapy at a weekly base due to physical impairment, lack of time or unwilling etc.

### Intervention

#### Experiment group

The subjects who are arranged to the experiment group will be intervened using the reminiscence therapy manual proposed by Watt and Cappeliez (2000). According to the manual, the group consisted of six weekly sessions of 90 min each. There will be about four people in each subgroup. During each weekly session, the memories recalled focused on a different theme. The themes are as follows: major branching points in your life, family life, your career or major life work, your loves and hates, stress experiences, the meaning of your life and belief. Five relative questions were set to help retrieve memory in each theme. We explain to participants that the memories of these themes should be related to experiences with a significant impact on their life. Also, we make a distinction between personal recollections and recollections of historical facts which are not the focus of the intervention [25].

Except for the first session, the other sessions share the same procedures, including: homework review and agenda development (10 minutes), relaxation and focusing on reminiscence (5 minutes), contact work (50 minutes), feedback to clients (15 minutes), assignment of homework (5 minutes), feedback to therapist and questions (5 minutes). The first session will begin with participants’ self-introductions to get to know each other. The therapist will offer information about his work and qualifications to get confidence and closer to the participants. Then he will explain some concepts used in the session (such as “round”), rationale for reminiscence therapy, the preparations of the each intervention and corresponding procedures.

During each therapy process, Contact Work will account for a large proportion. Contact Work is a one-to-one encounter between a single therapist and a client in the group setting [25]. The therapist will invite the participant to share his/her memory about the theme, which he/she is asked to prepare before the meeting. With the direction of the manual, reminiscence will be conducted structurally. The other group members are required to listen and give no comment or judgment unless therapist’s request at that moment. As another necessary element, homework is very important for the reminiscence therapy. Homework which is related to the theme of the next session is assigned at the end of the present session and will be reviewed at the beginning of the next session. There are several reasons for stressing these homework assignments. For the first, it can help the participants re-familiarize themselves with the memory and the context in which it occurred, makes them get involved into the therapy quickly, and uses the time of the session more efficiently. Secondly, we can use homework to assess the compliance of the participants. Lastly, it can facilitate participants to practice this skill.

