#### Control group

The participants assigned to the waiting-list as control group will be treated as before. We will keep in touch with them getting to know whether they are still available to be the member of the control group.

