### Statistical analysis

According to some previous researches, personal characteristics of the subjects may have an impact on the outcomes. Though the RCT design is adopted, the demographic data between the control group and the experiment group still should be considered. When the two groups do not match on demographic data, related statistical methods will be brought in to make up for this. In addition, the data of participants who are absent from the group session for four times or more and who turn to antidepressant or other non-pharmaceutical intervention before the end of the therapy will be excluded when analyses conducted [39].

SPSS 16.0 statistical packages will be used to conduct the data analyses. Paired *t* test will be used to detect the changes of the outcome measures within intervention or control group. Standardized change scores will be calculated by subtracting pre-test score from post-test score of intervention and dividing by the SD for all participants combined. A repeated measures analysis of covariance (ANCOVA) model will be used to evaluate the effects of intervention on continuous outcome variables that are available at each data collection point. The between-subjects factor is group (intervention group, control group) and the within-subjects factor is assessment phase (baseline, post-test, follow-up test). All statistical tests were two sided, and *p* values < 0.05 were considered significant. In addition, effect sizes (Cohen’s d) [52] will be computed based on the differences between the pre-and post-intervention (or follow-up test) means and the pooled variance.

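### Therapy is given in subgroups of about four, but the planned tests treat participants as independent; if outcomes correlate within subgroups, p-values will be somewhat too small

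*Protocol article*

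**What the plan says.** All references are to the Protocol article.

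- **Participants:** "A total of sixty subjects who fulfill the following inclusion and exclusion criteria will be recruited from the community". The allocation ratio is not stated.
- **Design:** the unit of randomisation is the person: "research assistant will open a sealed sequential randomization envelope for each participant".
- **Experiment group:** treatment is delivered in small groups over six weekly 90-minute sessions: "There will be about four people in each subgroup". The core of each session is individual work done in front of the others: "Contact Work is a one-to-one encounter between a single therapist and a client in the group setting". Homework review, relaxation and feedback fill the rest of the session.
- **Control group:** "The participants assigned to the waiting-list as control group will be treated as before". No groups are described for this arm.
- **Statistical analysis:** "A repeated measures analysis of covariance (ANCOVA) model will be used to evaluate the effects of intervention on continuous outcome variables". On the factors: "The between-subjects factor is group (intervention group, control group"). Here the word group means trial arm. The only other factor is assessment phase, with baseline, post-test and follow-up as levels. Paired t tests are planned within each arm. Tests are two-sided at 0.05.

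**The concern.** This is a partially nested design: one arm is clustered and the other is not. People who attend the same six sessions share a room, a therapist and each other's company, so their later scores may be more alike than scores from different subgroups. With arm and phase as the only factors, any such similarity stays in an error term that assumes independent participants. The standard error of the arm comparison is then too small. The paired t test in the therapy arm is affected more, because every participant in it belongs to a subgroup.

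At stake is the error rate of the main efficacy test, in a trial whose therapy arm rests on only seven or eight subgroups. This is not a detail left to a fuller document. The article states the model and its factors, and the point concerns what that stated model assumes.

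**Working it through.** **Inputs from the article:** 60 participants; subgroups of about 4; ungrouped controls; two-sided alpha 0.05; three assessment phases.

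**Assumed, because the article does not give them:** 1:1 allocation (30 per arm, so 30/4 = 7.5, that is 7 to 8 subgroups); correlation 0.5 between visits; ICC from 0 to 0.20. The null hypothesis is no average effect, with subgroup means varying around it.

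**Starting check.** The article gives no effect size, SD or power for its 60, so the sample size cannot be reproduced. The nominal alpha can: a simulated comparison of 30 with 30 at ICC 0 rejects in 4.98% of trials.

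**Formulas.** With m = 4, the design effect in the therapy arm is DE = 1 + (m − 1) × ICC = 1 + 3 × ICC. In the control arm it is 1. At 1:1 the variance of the arm difference is multiplied by VIF = [1 + (1 + 3 × ICC)]/2 = 1 + 1.5 × ICC. The actual alpha is about 2 × [1 − Φ(1.96/√VIF)]. For the paired test in the therapy arm, DE takes the place of VIF. The formulas carry over to pre-post change because, at correlation 0.5, the variance of a change is 2 × (1 − 0.5) = 1 times that of a single score.

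*Example, ICC 0.10:* VIF = 1.15, 1.96/√1.15 = 1.83, alpha about 6.8%. Therapy arm alone: DE = 1.30, 1.96/√1.30 = 1.72, alpha about 8.6%.

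**Simulation of the planned tests:** 40,000 null trials per ICC. The formula columns are the analytic check.

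| ICC (assumed) | VIF | Group-by-phase, formula | Group-by-phase, simulated | DE | Therapy-arm paired t, formula | Therapy-arm paired t, simulated | Effective therapy-arm n (30/DE) |
|---|---|---|---|---|---|---|---|
| 0 | 1.00 | 5.0% | 4.8% | 1.00 | 5.0% | about 5% | 30 |
| 0.02 | 1.03 | 5.4% | 5.3% | 1.06 | 5.7% | 5.8% | 28.3 |
| 0.05 | 1.075 | 5.9% | 5.5% | 1.15 | 6.8% | 6.5% | 26.1 |
| 0.10 | 1.15 | 6.8% | 6.6% | 1.30 | 8.6% | 8.1% | 23.1 |
| 0.20 | 1.30 | 8.6% | 8.7% | 1.60 | 12.1% | 11.9% | 18.8 |

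The simulation error at 40,000 runs is √(0.05 × 0.95/40,000) = 0.11 percentage points. A separate simulation of the group-by-phase test gave 5.7%, 6.3% and 8.4% at ICC 0.05, 0.10 and 0.20, so the results are reliable to a few tenths of a point.

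Across ICC 0.05, 0.10 and 0.20 the planned standard error is 1/√VIF = 0.96, 0.93 and 0.88 of the correct one. A test that allowed for the subgroups stayed near 5%.

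**The case against.** **The session format limits group interaction.** Contact work takes 50 of the 90 minutes and is one-to-one, and listeners may comment only if the therapist asks. This stands in part. It makes an ICC as high as 0.20 less plausible, but members still share the sessions, so it does not establish an ICC of zero. Likewise, if one therapist treats every subgroup, the therapist does not contribute to differences between subgroups, but the shared membership still does.

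**The inflation is conditional and moderate.** This stands. At ICC 0 the planned tests are valid, and at 0.02 the excess is a few tenths of a point.

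**A clustering term is hard to estimate from seven or eight subgroups.** This also stands and shapes the fix. In simulation the analysis-of-variance estimate of the subgroup variance was zero or negative in 44% of trials at a true ICC of 0.05, and in 33% at 0.10. At a true ICC of 0.05, 95% of the ICC estimates lay between about −0.24 and 0.41.

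**Stronger readings that the article does not support.** A reader might infer that the false-positive rate certainly exceeds 5%; with no ICC given, that cannot be said. A reader might infer that reported confidence intervals will be too narrow, but the section announces p-values and Cohen's d, not intervals. A reader might also take error rates from a two-sample t test or a baseline-adjusted comparison at one visit (the latter gives about 6.2%, 7.1% and 9.3% at ICC 0.05, 0.10 and 0.20). Neither is planned: baseline is a level of the phase factor. Finally, it has not been shown that a positive result would rest on one or two good subgroups. A standard error 4% to 7% too small (ICC 0.05 to 0.10) changes only borderline results.

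**Conclusion.** The point holds in conditional form. The stated analysis ignores clustering that the stated delivery creates in one arm. Over an assumed ICC of 0.02 to 0.20, the nominal 5% becomes about 5.3% to 8.7% for the group-by-phase test and about 5.8% to 11.9% for the therapy-arm paired t test. The conclusion rests on a positive ICC, 1:1 allocation, a correlation of 0.5 between visits, and a subgroup effect present at the post-treatment visits. The direction is secure whenever the ICC is positive; the size is not known. The change should be made because it is cheap and the subgroup number may not be recoverable later, but the problem would not by itself invalidate a clear result.

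**What to change.** 1. Record each participant's therapy-subgroup number while therapy is being delivered.
2. Base the between-arm test on a partially nested mixed model: fixed effects for arm, phase and their interaction; a random subgroup effect at the post-treatment visits in the therapy arm only, with each control as a separate unit; and Satterthwaite or Kenward-Roger degrees of freedom. Check that the named software release offers the chosen method.
3. State in advance that the subgroup term stays in the model whatever the ICC estimate, since a zero estimate is common with so few subgroups and is not evidence of independence.
4. Take the therapy-arm change from the same model, or label the paired t test there as descriptive.
5. Report the ICC with its interval, and say that seven or eight subgroups estimate it poorly.

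The cost is one extra variable and a changed model statement, slightly less precision and fewer degrees of freedom. Treatment, recruitment and visits are unchanged.

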#### Control group

The participants assigned to the waiting-list as control group will be treated as before. We will keep in touch with them getting to know whether they are still available to be the member of the control group.

### Data collection and outcome measures

The main data will be collected using some standardized instruments with demonstrated validity and reliability which will be described as follows. Data collection will occur on screening (as for baseline or pre-test), after intervention immediately (as for post-test), and three months after the intervention (as for follow-up). In addition to these measures, we will use some scales developed by ourselves to collect data. These scales are used to assess the participants’ attitude towards the intervention. Moreover, the therapist will be given the scales used to rate participants’ compliance after each session.

#### Primary outcome: Depressive symptoms

Symptoms of depression will be measured with the GDS. GDS is a self-rated scale consisting of 30 items with response of “yes” or “no” to measure a person’s emotional state in the past week. The entire scores ranges from 0 to 30, and higher scores represent more severe level of depression. Generally, scores from 11 to 20, from 21 to 30 indicate mild, severe depression respectively [44]. The GDS designed specifically for the elderly, and it has been proved with high reliability and validity. According to the research of Yesavage and Brink (1982), the Cronbach’s alpha coefficient was 0.94 and the test-retest reliability after one week was 0.85 among twenty participants [45].

